### Interim analyses {21b}

N/A. No interim analyses are planned.

### Methods for additional analyses (e.g., subgroup analyses) {20b}

N/A. No additional analyses are planned.

### Methods in analysis to handle protocol non-adherence and any statistical methods to handle missing data {20c}

Protocol violations after randomization will be listed in the clinical study report, tabulated by subject and recruitment site. We will perform intention-to-treat analyses with a “missing=failure” strategy to the management of missing data.

Sensitivity analyses will be performed for the missing data management: multiple imputation, available data, and maximum bias.

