### Trial design {8}

This is a randomized, double-blinded, paralell group, non-inferiority controlled trial.

The trial protocol conforms with the Consolidated Standards of Reporting Trials (CONSORT) Statement. The trial design and protocol adhere to the Standard Protocol Items of the Recommendations for Interventional Trials (SPIRIT) criteria.

The study aims to compare the efficacy of endodontic treatments conducted in a single visit using ultrasonic irrigant activation and in two visits also using ultrasonic irrigant activation, with and without the use of calcium hydroxide dressing, in lower molar teeth with asymptomatic apical periodontitis (Fig. 1, “Study flowchart”).

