#### Exclusion criteria

Patients may not participate in the study if they are as follows: (1) teeth with extensive coronary destruction that makes direct restoration with composite resin unfeasible, (2) calcified teeth, (3) teeth with incomplete root formation, (4) teeth with persistent exudation, (5) teeth with anatomical complexities that prevent endodontic treatment in a single visit, (6) teeth recommended for endodontic retreatment, (7) teeth with advanced periodontal pocket, and (8) teeth in which foraminal patency is not obtained.

Patients who present a profile that fits to that described in the inclusion and exclusion criteria will then be referred for evaluation by other examiners ([name], [name], and [name], experts in Endodontics for more than 15 years), for confirmation of diagnosis and treatment planning, if necessary. Patients who do not fit the required profile will be forwarded to the health unit of origin. All the steps of interviews and clinical examination necessary to complete the diagnosis will be carried out by the examiners who will perform the treatment.

Patients with systemic diseases (diabetes, transplants, heart disease, liver failure, and kidney failure) and immunodepressed patients are prohibited during the trial as these conditions can affect the oral functions.

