### Relevant concomitant care permitted or prohibited during the trial {11d}

Patients are prohibited to take any anti-inflammatory or antibiotic medication during their participation at this research study.

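### For a trial declared as non-inferiority, the non-adherence section provides a violation listing and intention-to-treat but no supportive per-protocol analysis, so crossover between arms would usually favour the claim unseen

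*Protocol article*

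**What the plan says.** The Trial design section {8} states: "This is a randomized, double-blinded, paralell group, non-inferiority controlled trial".

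The section on non-adherence and missing data {20c} sets out three things:

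- On violations: "Protocol violations after randomization will be listed in the clinical study report, tabulated by subject and recruitment site".
- On the analysis set: "We will perform intention-to-treat analyses with a “missing=failure” strategy to the management of missing data".
- On sensitivity: "Sensitivity analyses will be performed for the missing data management: multiple imputation, available data, and maximum bias".

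All three sensitivity analyses deal with absent outcomes. The available-data analysis leaves out teeth without an outcome; it does not leave out teeth that were treated differently from their allocation. The article names no per-protocol or as-treated set in any section.

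The Main outcome analysis section compares success across the three groups with a Kruskal-Wallis test at the 5% level. No non-inferiority margin is stated anywhere. The 20% in Sample size details is called an effect size.

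**The concern.** In a superiority trial, dilution under intention-to-treat works against the claim, which is why that analysis is regarded as cautious. In a non-inferiority trial it usually works for the claim. These arms differ in the number of visits and in whether a dressing is placed. A tooth that receives another arm's treatment therefore carries that treatment's prognosis into its allocated arm and narrows the observed gap.

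Two deviations fit this pattern directly: a tooth allocated to two visits without dressing that is dressed, and a single-visit tooth converted to two visits with dressing. Such a tooth can have an observed 24-month outcome, and then neither the missing-as-failure rule nor the missing-data sensitivity analyses would pick up the effect.

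Some deviation after allocation is foreseeable from the article. Sequence generation {16a} places randomisation before all clinical procedures, while the exclusion criteria include failure to obtain foraminal patency, which is learned only during canal work. Section {11b} lists poor compliance as a reason to discontinue or modify treatment. At stake is a claim that a single visit, or omitting the dressing, is no worse, when part of the apparent similarity comes from teeth that were not treated that way.

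**Working it through.** **Inputs from the article.** 70 teeth per arm (Sequence generation {16a}).

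**Inputs assumed, because the article does not give them.** Reference success at 24 months 80%, with two visits and dressing as the reference; a margin of 20 points, borrowed from the 20% effect size, with 15 points as an alternative; one-sided 0.025; a true deficit exactly at the margin; a share c of single-visit teeth receiving the reference treatment, from 0 to 20%. Teeth are treated as independent. With 210 teeth in 150 patients they are clustered, so real precision is lower.

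The plan has no figure of its own on this point to reproduce.

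**Formulas.**

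- Observed deficit: d = margin × (1 − c)
- Observed success in the single-visit arm: pt = 0.80 − d
- SE = √[0.80 × 0.20/70 + pt(1 − pt)/70]
- False non-inferiority = Φ[(margin − d)/SE − 1.96]

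**Margin 20 points.**

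| c | d | pt | SE | (margin − d)/SE | False non-inferiority |
|---|---|---|---|---|---|
| 0 | 0.200 | 0.600 | 0.0756 | 0 | 2.5% |
| 2% | 0.196 | 0.604 | 0.0755 | 0.053 | 2.8% |
| 5% | 0.190 | 0.610 | 0.0754 | 0.133 | 3.4% |
| 10% | 0.180 | 0.620 | 0.0752 | 0.266 | 4.5% |
| 20% | 0.160 | 0.640 | 0.0747 | 0.536 | 7.7% |

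**Margin 15 points.** The same steps give 2.5% at c = 0, 3.9% at 10% and 6.0% at 20%.

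**Other success rates.** With the 20-point deficit at 85 v 65% or 90 v 70%, the rate reaches up to 4.9% at 10% crossover and up to 9.2% at 20%.

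**On the test the article names.** A simulation of the three-arm Kruskal-Wallis test (40,000 runs, 70 teeth per arm, true success 60/80/80%, a share of the 60% arm receiving an 80% treatment) gives a non-significant result in 22% of trials with no crossover, 30% at 10% and 40% at 20%. If non-significance were read as equivalence, dilution would push the same way.

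**Cost of a smaller set.** With 80% success in both arms, a 20-point margin and one-sided 0.025, power is Φ[0.20/√(2 × 0.16/n) − 1.96]. That is 84% at n = 70, 80% at n = 63 (10% removed) and 75% at n = 56 (20% removed).

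**The case against.** The strongest reply has four parts.

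**Article versus full plan.** The article says intention-to-treat will be done; it does not say that nothing else will. A supportive per-protocol set could stand in a document not shown. A reader might infer from "N/A. No additional analyses are planned" that such an analysis is ruled out. That sentence answers the item on additional analyses such as subgroups {20b}, and {20c} itself goes on to plan sensitivity analyses, so it cannot exclude everything else. This part stands: the documents do not show that per-protocol analysis was rejected. What remains is that the section devoted to non-adherence states its handling, and what it states does not suit the declared design.

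**No non-inferiority test to bias.** There is no margin, interval rule or non-inferiority test, and for a test of difference intention-to-treat is the cautious choice. This also stands in part. The point takes full effect only once a margin and decision rule exist, although the simulation shows the same direction if non-significance is over-read.

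**Crossover may be rare.** The operators are experienced specialists who open the envelope at the moment of intervention, and the criteria already exclude "teeth with anatomical complexities that prevent endodontic treatment in a single visit". At 2 to 5% crossover the inflation is slight.

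**Not every violation blurs the arms.** A reader might take all violations to pull the arms together. The documents do not support that. A two-visit tooth that is never completed has not received single-visit treatment and may end as failed or missing. A single-visit tooth finished later without dressing has received the third arm's treatment, not the dressed reference. The rule "Patients are prohibited to take any anti-inflammatory or antibiotic medication during their participation at this research study" applies to all arms, and a breach of it could move any arm either way.

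**Conclusion.** The point holds in a limited form. The trial is declared as non-inferiority, and its non-adherence section offers a listing, intention-to-treat and missing-data sensitivity analyses, with nothing that looks at treatment received. Teeth given another arm's treatment would usually shrink a true deficit. Under the stated assumptions the false non-inferiority rate rises from a nominal 2.5% to between 2.8% and 3.4% at 2 to 5% crossover, and to 4.5% and 7.7% at 10% and 20%. Margin, success rate and crossover rate are all assumed, and dilution towards no difference is the usual direction, not a certainty.

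A reader might go further and ask that both the intention-to-treat and the per-protocol interval clear the margin. The documents do not force that. It would give a veto to a set that is no longer fully randomised, and it costs power. The absent margin and non-inferiority test are a separate fault that comes first, and correcting them alone would not resolve this one.

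**What to change.** Once the margin and non-inferiority test are defined, add the following to section {20c}:

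- A prespecified supportive per-protocol analysis of the same primary contrast, in teeth treated in the allocated number of visits and with or without dressing as allocated.
- Classification of each tooth blind to outcome.
- Violations tabulated by arm as well as by subject and site.
- The per-protocol result reported beside intention-to-treat, with any disagreement discussed before non-inferiority is claimed.

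The cost is one definition and one further analysis; violations are already to be tabulated by subject. The per-protocol set will be smaller and open to selection, since deviation may be related to prognosis, so intention-to-treat stays the main analysis.

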## Sample size and statistical methods

### Sample size details

The required sample size was calculated based on the preliminary outcome parameter of success, in a sequential approach, with each clinical case (tooth) serving as the statistical unit. Clinical studies that allow us to estimate, by means of CBCT, the repair index (complete absence of periapical radiolucency), therefore the success, after endodontic treatment of teeth with apical periodontitis and periradicular lesion, state that it is necessary to have a follow-up of at least 2 years to determine the success or failure of the treatment [22, 23]. After the first year of follow-up, post-endodontic treatment, it is still possible to observe the presence of periapical radiolucency in 52 to 84% of cases [1, 24, 25]. The sample will consist of 210 mandibular molars (first or second molars), based on statistical sample calculation, considering a power of 80%, an alpha value of 0.05, and an effect size of 20%. All patient characteristics at the beginning of treatment, such as age, gender, lesion size, among others, will be considered in the statistical analysis, in order to confirm the randomization of groups and the possible confounding effect of these characteristics.

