#### Main outcome analysis

The inter-group comparison of success rates will be analyzed using the Kruskal-Wallis test at 5% of the level of significance. For the missing data, the last observation carried forward (LOCF) method will be adopted to fill the validity analysis.

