## Discussion

Endodontic treatment consists of a type of therapy of considerable complexity due to factors such as the anatomical variety of the root canal system, the presence of curvature of the main root canal, branches of other canals, isthmuses, areas inaccessible to the endodontic instrument [5, 7], and the dentin permeability itself, associated with the possibility of infection of this system [9, 15]. These anatomo-structural characteristics of the root canal system, accompanied by an infectious process, make it necessary to develop techniques that allow for a more predictable cleaning and disinfection of this environment of difficult visibility and access [9]. Cases of apical periodontitis can often bring additional challenges to professionals, due to the presence of periradicular lesion, which characterizes a high level of microbial contamination, in the form of bacterial biofilm, requiring a highly efficient chemical and mechanical action that is able to eliminate the greatest possible number of microorganisms from the root canal system, allowing the organism to respond favorably in the tissue healing and repair process [2]. Inappropriate planning or management of endodontic treatment of a tooth with asymptomatic apical periodontitis can lead to a flare-up, the need for re-intervention, or retreatment [3]. Thus, the use of chemomechanical root canal preparation protocols through engine-driven rotary instrumentation with nickel-titanium (NITi) instruments, which provide faster preparation, associated with the use of irrigating solutions, activated by ultrasound, and intracanal medication, both with high antibacterial potential, is increasingly suggested for the treatment of such pathology, with the objective of promoting a level of disinfection that allows healing (the repair of periradicular tissues) and the absence of postoperative symptoms [26, 27]. However, the option for endodontic treatment in a single visit, where intracanal medication is not used, for a minimum period of 7 days, between visits, is questioned by a considerable number of studies [13–15], often for fear that remaining bacteria after chemomechanical preparation may cause some kind of injury and that the patient may present postoperative pain [17–19]. Obturating a tooth with asymptomatic apical periodontitis in a single visit characterized as an unreliable or unsafe procedure mainly in results of in vivo studies in an animal model [13, 14] or in in vitro studies [15], although the systematic reviews [16–18] and randomized clinical trials [1, 19, 20] show that the results are similar for postoperative pain and cure rate when endodontic treatments conducted in a single visit and in multiple visits are compared. These studies emphasize that the criteria used during chemomechanical preparation are considered more efficient when associated with ultrasound during endodontic treatment. By using irrigating solutions with greater antimicrobial potential associated with methods that promote the agitation of these substances inside the main canal for longer periods of time and with greater amounts of solution, it allows them to reach dentinal tubules or regions further away from the main canal and that ultrasonic cavitation promotes a disruption of the bacterial biofilm, promoting superior clinical results [7] and, consequently, increasing the acceptance of the single visit as a form of treatment for asymptomatic apical periodontitis among professionals. Furthermore, the determination of chemomechanical preparation protocols, based on criteria that enhance the antimicrobial action of irrigating solutions, would allow the standardization of these protocols for scientific purposes, making comparative studies more reliable [16]. Although the successful elimination of bacteria from the root canal system remains the most important therapeutic goal in Endodontics [2], there is no consensus on the most effective clinical approach, raising doubts about what would be the best treatment model to be followed [1]. The present study aims to compare a single-visit endodontic treatment with a two-visit treatment in cases of asymptomatic apical periodontitis using four parameters for outcome analysis: first, clinical success through periradicular lesion repair. It is very important that the clinician knows the time needed to verify the complete repair of a periradicular lesion in a case of apical periodontitis. This knowledge will allow the professional, at the end of the treatment, to guide the patient about the healing process, as well as allow a more objective assessment of a treatment performed by another professional, reducing misdiagnoses of failure and subsequent retreatment proposals. Periapical radiography is the most commonly used method to assess the cure rate in apical periodontitis [1, 13, 16]; however, the two-dimensional image does not represent a real evaluation because it masks results [24], so the proposal is also to evaluate the results through CBCT, comparing with periapical radiography before and after 2 years of follow-up. Second, postoperative pain will be assessed during periods of 24, 48, and 72 h and 7 days. Postoperative pain to endodontic treatment may be related to several factors such as host response to treatment, microbial pathogenicity, or extrusion of debris beyond the foramen caused by inadequate instrumentation [19]. Third, subjective results will be evaluated, that is, those reported by patients. This is relevant, as it brings the subjective perception that the patient had or has about the endodontic treatment and confirms or not the common sense that endodontic treatment and pain are synonymous, promoting behavior changes on the patient’s future attitudes in the next visits when the need arises, to perform a new endodontic treatment. Finally, the study will assess the patient’s satisfaction rate with the treatment performed. This is relevant, as the patient will be able to assess the experience of undergoing endodontic treatment and report their degree of satisfaction after completion of the treatment. Despite all the objectives presented, this study also has limitations. Firstly, the instrumentation and irrigation protocol used in this study, despite being within the best parameters of current endodontic therapy [9, 26, 27], has variations in the time of ultrasound use during cavitation and also in the amount of irrigant made of 5.25% NaOCl with a volume higher than those tested in other studies. Even though group 3 will not have intracanal medication placed, both groups 2 and 3 will have the same number of days between visits in order to avoid confounding variables that could interfere in the study outcome results. Although there are studies in the form of systematic reviews [16–18] and randomized clinical studies [1, 19, 20], showing similar results, regarding the success rate and postoperative pain in cases of endodontic treatments completed in a single visit and in multiple visits in teeth with apical periodontitis, there is no consensus on the instrumentation and irrigation protocols to be used. The same thing happens in vitro studies [15] and in vivo studies in an animal model [13, 14], and there is also no consensus regarding the instrumentation and irrigation protocols. In most of these studies, irrigation protocols describe the use of NaOCl solutions with active chlorine concentrations less than 5.25% [19, 27]. Systematic reviews criticize the volume and time that the irrigating solution remains inside the root canal system [16, 17]. Furthermore, some studies do not use ultrasound as an irrigation intensifying agent [7, 13] and still do not specify the volume of the chemical substance used during treatment [4]. This variety of protocols promotes different results in the studies and, consequently, divergences of opinions and clinical approaches. Secondly, in clinical studies, there is the difficulty of following the patient for long periods after the end of treatment [1], which creates the need to think of special approaches to try to ensure the patient’s permanence in the study, such as offering free oral health promotion actions, for example. Thirdly, the sample size is also considered a complicating factor, since the numbers used in the studies found are quite different, which points to questionable results [14]. Lastly, this study will be conducted in lower molar teeth, which have more complex anatomy, are more affected by periodontal disease, and also because they are the most standardized teeth in randomized clinical trials [28].

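### In a trial declared non-inferiority, counting missing as failure in every arm dilutes a true deficit when loss is similar across arms, so it should not be the lead rule for the repair comparison

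*Protocol article*

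**What the plan says.** Trial design {8} of the Protocol article states: "This is a randomized, double-blinded, paralell group, non-inferiority controlled trial". Under Outcomes {12}, success requires full repair at two years confirmed by CBCT, so a tooth without a 24-month examination has no primary result.

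Section {20c} sets the rule for such teeth: "We will perform intention-to-treat analyses with a “missing=failure” strategy to the management of missing data". It names no exception for any arm. It then adds: "Sensitivity analyses will be performed for the missing data management: multiple imputation, available data, and maximum bias".

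The section Main outcome analysis gives a different rule: "For the missing data, the last observation carried forward (LOCF) method will be adopted to fill the validity analysis". The test named there is one of difference: "The inter-group comparison of success rates will be analyzed using the Kruskal-Wallis test at 5% of the level of significance".

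The article states neither a margin nor an expected loss rate. The Discussion does foresee loss, noting that in clinical studies "there is the difficulty of following the patient for long periods after the end of treatment".

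**The concern.** The objective is periradicular repair over two years. Scoring every missing 24-month result as failure replaces this with a composite: repaired and also came back for the scan. In a superiority trial, failures added alike to all arms pull the difference towards zero and make a positive claim harder, which is why the rule is often called conservative. In a non-inferiority trial a difference nearer zero is what supports the claim. Where single visit, or no dressing, is truly worse and loss is similar across arms, the rule hides part of the deficit.

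At stake is a false conclusion that the dressing visit can be dropped, in a trial whose primary result comes two years after treatment. Absolute success rates would also be understated by the factor (1−L).

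**Working it through.** **Inputs from the article.** Non-inferiority design (Trial design {8}). Missing=failure in all arms ({20c}). 70 teeth per arm, from 210 teeth in 150 patients (Sequence generation {16a}). The sample size was set "considering a power of 80%, an alpha value of 0.05, and an effect size of 20" per cent.

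**Inputs that are assumed.** Margin 20 points (the stated effect size, which the article does not call a margin). True success 80% in the dressing arm, taken as the reference, and 60% in the arm compared with it. Loss of 10, 20 and 30%, unrelated to outcome. Teeth independent. One-sided 2.5% test from a Wald confidence limit.

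**The plan's own figure.** The 210 teeth cannot be uniquely reproduced, because no base success rate is given. Among other choices, 67% vs 87% in a two-sided test gives 69 per arm, and non-inferiority with both rates at 77% and a 20-point margin gives 70 per arm. The sample size therefore does not reveal the intended margin or rates.

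**Effect of the rule.** Observed rate = p(1−L). Observed deficit = pC(1−LC) − pT(1−LT), where C is the dressing arm and T the arm compared with it. If LC = LT = L, this is (1−L)(pC − pT).

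**Worked case, 20% loss in both arms.** Rates 0.80 × 0.80 = 0.64 and 0.60 × 0.80 = 0.48, so the observed deficit is 0.16. SE = √[(0.64 × 0.36 + 0.48 × 0.52)/70] = √(0.48/70) = 0.0828. The shift is (0.20 − 0.16)/0.0828 = 0.483. False non-inferiority ≈ P(Z > 1.96 − 0.483) = 7.0%. Exact binomial enumeration gives 6.8%.

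| Equal loss | Observed deficit (points) | False non-inferiority, missing=failure (exact) | Same, available data |
|---|---|---|---|
| 0% | 20 | 2.5% | 2.5% |
| 10% | 18 | 4.2% | 2.5% |
| 20% | 16 | 6.8% | 2.6% |
| 30% | 14 | 10.7% | 2.5% |

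The last column shows that the inflation comes from the rule and not from having fewer teeth. At 20% loss the rate is 6.8% to 7.5% for reference success rates from 50% to 90%. With a 10-point margin and a true 10-point deficit it is 4.2% to 4.6% for reference rates of 70% to 90%.

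**If non-inferiority is read from a non-significant test of difference.** Pairwise power for 80% vs 60% with no loss: SE = √[(0.16 + 0.24)/70] = 0.0756, 0.20/0.0756 = 2.646, power 0.75. At 20% loss under missing=failure: 0.16/0.0828 = 1.932, power 0.49. At 20% loss with available data, 56 teeth per arm: SE = √(0.40/56) = 0.0845, 0.20/0.0845 = 2.366, power 0.66. The fall from 0.75 to 0.66 is due to lost teeth; only the fall from 0.66 to 0.49 is due to the rule.

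**Unequal loss** (true 80% vs 60%, margin 20, exact):

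| Loss, dressing arm | Loss, single visit | Observed deficit (points) | False non-inferiority |
|---|---|---|---|
| 15% | 20% | 68 − 48 = 20 | 2.3% |
| 10% | 20% | 72 − 48 = 24 | 0.6% |
| 20% | 10% | 64 − 54 = 10 | 22% |

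With no true difference (both 80%), 10% loss in the dressing arm and 20% in the single-visit arm create a deficit of 72 − 64 = 8 points.

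**Truly equal arms, equal loss.** With both rates at 80% and a 20-point margin, the chance of showing non-inferiority falls from 84% with no loss to 69% at 20% loss under missing=failure (76% with available data).

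**The case against.** A reader might infer that dropout always pushes this trial towards finding single visit no worse. The documents do not support that. The dilution needs similar loss across arms, loss unrelated to outcome, and a true deficit. A five-point imbalance in loss can cancel it, a ten-point imbalance can reverse it, and between truly equal arms the rule makes non-inferiority harder to show. Similar loss is still a reasonable base case, because the 6-, 12- and 24-month schedule is the same in every arm. Unequal loss does not rescue the rule either, since the result then depends on attendance.

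The error rates belong to a non-inferiority test that the article does not describe: its named test is Kruskal-Wallis, and no margin is stated. This objection stands, so the figures only illustrate. The direction is the same if the conclusion is drawn from a non-significant difference test.

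It is also not settled that missing=failure governs the primary result, because Main outcome analysis names last observation carried forward. This stands too, and the two sections have to be reconciled. The concern applies in full if {20c} governs.

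Finally, {20c} already plans "multiple imputation, available data, and maximum bias" as sensitivity analyses, which would expose the dilution. They would not change the lead result.

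A reader might also fault the plan for naming no per-protocol analysis and no rule that analyses must agree. The article does not exclude either, and a condensed article may leave both to the full protocol or analysis plan. They form no part of this point.

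**Conclusion.** The concern holds in a limited form. As the lead rule for the repair comparison, missing=failure in every arm is poorly suited to a declared non-inferiority design. With similar loss that is unrelated to outcome, it multiplies a true deficit by (1−L) and raises the risk of a false claim. With differential loss it mixes attendance with repair, in either direction.

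Under the assumptions listed, the nominal 2.5% error becomes about 4.2%, 6.8% and 10.7% at 10, 20 and 30% equal loss. The size in this trial cannot be fixed, because margin, success rates and loss are not stated and teeth within a patient are not independent. The algebra of the dilution depends on none of these except equal loss unrelated to outcome. The change should be made: the bias comes from a stated rule, and the remedy is cheap.

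**What to change.** 1. Reconcile Main outcome analysis (last observation carried forward) with {20c} (missing=failure), and state one primary missing-data rule.
2. Make the multiple imputation already listed in {20c} the lead analysis for the repair comparison, done by arm, using baseline lesion size and the 6- and 12-month PAI. Teeth already known to have failed by the plan's own clinical and radiographic criteria in Outcomes {12} stay failures and are not imputed.
3. Move missing=failure to the sensitivity analyses.
4. State the direction of the maximum-bias analysis so that it works against the arms claimed non-inferior: missing as failure in groups 1 and 3, missing as success in the dressing group.

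The cost is an amendment to two sections and some analysis time. No patients, visits or measurements are added. The drawback is that multiple imputation assumes data missing at random given the variables used; the directed maximum-bias analysis tests how far the conclusion depends on that.
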